**ABSTRACT**

Cervical cancer and HIV are intersecting epidemics that both disproportionately affect low-income women; the impact of the socioeconomic disparity and biologic synergy of these two diseases is seen dramatically in Kenya, where cervical cancer is the most common cancer killer. HIV-infected women are at increased risk for the development of cervical precancer and cancer, develop more aggressive lesions and are affected at younger ages. Although screening for and treatment of precancer has reduced the incidence of cervical cancer to close to zero in resource-rich countries, strategies are costly and not available in most resource-limited countries. Novel testing and treatment methods that can be carried out in low-resource settings are urgently needed to prevent cervical cancer in these settings, especially among HIV-infected women. Using a cross-sectional study design, we propose to test two potentially low-cost and effective cervical cancer screening methods: **visual inspection with acetic acid** (VIA) and **protein biomarkers** expressed in the presence of cervical dysplasia, neither of which have been well-studied in HIV-infected women. We will also randomize a small subset of women to undergo VIA compared to **Visual Inspection with Lugol's Iodine (VILI**) to compare the test characteristics of these two screening exams. In addition, remarkably little is known about the potential **impact of the presence, diagnosis and treatment of HPV-related dysplasia on HIV genital shedding, a major risk factor for HIV transmission**. To explore the impact of the presence, diagnosis and treatment of HPV-related cervical dysplasia on HIV-1 in genital secretions, we will compare the levels of HIV-1 RNA found in the cervicovaginal secretions of women with no evidence of cervical dysplasia to levels in women with high-grade cervical dysplasia. We will also compare the levels of HIV-1 RNA prior to and after cervical biopsy as well as up to 14 weeks after standard treatment for cervical dysplasia using loop electrosurgical excision procedure (LEEP). Results from this study will inform the prioritization and design of safe, effective and low-cost cervical cancer screening and prevention programs for HIV-infected women in resource-limited settings.

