| Will undergo LEEP for CIN2/3 at one of the FACES study clinics in Kisumu | Allows baseline specimen collection and ensures the quality and standard of the LEEP |
| Willing to remain abstinent from sexual activities for four weeks post-LEEP and for three days prior to each follow-up study visit | Reduces risk of post-LEEP bleeding and infection. Reduces potential semen contribution to genital HIV-1 viral load measurements. |
| Exclusion Criteria | Rationale |
| Pregnant | May increase false positive rate of VIA^75^ |
| Clinical evidence of cervical or pelvic infection:   - Muco-purulent discharge - Cervical friability - Cervical motion tenderness found on pelvic exam in symptomatic women | May increase false positive rate of VIA^75^ |
| Cervical cancer screening at FACES within past 12 months | May influence clinician interpretation of results |
| Prior or current history of cervical surgery, dysplasia or cervical cancer | May influence test characteristics of colposcopy and VIA |
| Unsatisfactory VIA | Woman would require alternative screening method (cytology, colposcopy or endocervical sampling) per WHO protocol^74^ |
| *Additional Criteria for Specific Aims 3 & 4:* |  |
| Laboratory evidence of cervical infection:   - NAAT for Gonorrhea or Chlamydia - Wet mount showing bacterial vaginosis, candida or trichomonas | Concomitant sexually transmitted infections can increase the risk of HIV-1 genital shedding |

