We will sequentially recruit and enroll eligible women for all specific aims. There will be three separate consent forms (Appendix A, B and L). Screening and informed consent for participation in the studies involving VIA or VILI, colposcopy and specimen collection (S.A. 1, 2 and 3) will take place in a private gynecologic exam room prior to pelvic exam. Because satisfactory visual exam or clinical evidence of cervical or pelvic infection will only become evident after exam, participant numbers will be assigned after VIA and colposcopy. Women who are unsure about enrollment and would like time to consider will be given an information sheet (Appendix C) and may return for enrollment at a later date. VIA in these women will be deferred until their next visit. Eligibility and informed consent for the post-LEEP genital shedding sub-study will take place at a clinical visit, prior to their LEEP procedure. Women will be given an information sheet specific to this part of the study, in addition to the normal clinical materials in use that explain the LEEP procedure (Appendix D).

Statistical Considerations and Sample Size Calculation

**Specific Aim 1:** To calculate a sensitivity of 75% with a confidence interval of 5% in both directions and a two-sided alpha of .05, we will need to complete sequential VIA and colposcopy in ***1800* women**.^83^

To determine a specificity of 80%, with a confidence interval of 5% in both directions and a two-sided alpha of .05, we calculate that we will need to examine 400 women. Because the scientific outcome of specificity is most important, we will use the estimate of 1,800 women (900 VIA and 900 VILI to account for laboratory and sampling error) to power our study.

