We propose a ***cross-sectional*** study to evaluate this specific aim. Each participant will undergo a VIA or VILI with specimen collection for p16^INK4a^ and HR-HPV and colposcopy by a different clinician during a single clinic visit. The study clinician performing the colposcopy will be blinded to the results of the VIA or VILI. For women in the VILI arm, the colposcopy will be performed first in order to eliminate any interference with colposcopy interpretation from the iodine staining. Biopsy decisions will be made at the time of colposcopy, but deferred until after the VILI. Any woman with cervical lesions suspicious for dysplasia seen at the time of colposcopy will undergo biopsy. Colposcopy will be used as the reference standard for presence or absence of CIN2/3, with biopsy results being the final diagnosis when available. Women with a normal colposcopy without biopsy will be considered to have no disease.Specific Aims 1, 2, 2a and 2b)

We propose a **prospective cohort** study using a subset of women identified from the cross-sectional study in Specific Aims 1 and 2a to evaluate specific aim 2c during a one-year follow-up visit. We will recruit women for this follow-up study who participated in the pilot p16^INK4a^ ELISA study (Aim 2a) and had normal colposcopy or CIN1. In a single visit, each participant will undergo a VIA with specimen collection for p16^INK4a^ and HR-HPV followed by colposcopy and biopsy if needed.

We propose a ***case-control*** study to measure and compare the presence and quantity of HIV-1 RNA in the cervicovaginal specimens of women with biopsy-confirmed CIN2/3 (cases) and age-matched women without evidence of cervical disease as measured by negative VIA (controls). We will compute the odds ratio for HIV-1 detection and compare log transformed mean viral loads between cases and controls. (Specific Aim 3)

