**ETHICAL CONSIDERATIONS**

Human Subjects Involvement and Characteristics

The study described in this proposal will involve a total of around 1,800 HIV-infected women receiving care at the FACES clinics in Kisumu, Kenya. Women will be included in the study for the cross-sectional validation study if they are: 1) 25 years or older 2) not pregnant 3) accept cervical cancer screening 4) have a satisfactory Visual Inspection with Acetic Acid (VIA). Participants will be recruited for the prospective follow-up study (Specific Aim 2c) if they meet the above criteria, and were found to have normal colposcopy or CIN1 upon initial screening with p16^INK4a^ biomarker measurement. Participants will be recruited for the prospective post-LEEP HIV-1 shedding study if they meet the above criteria, have undergone LEEP for treatment of CIN2/3 and agree to remain abstinent for three days prior to each of the follow-up visits. To participate in any of these study activities, women must be willing and able to participate, be able to sign or mark a consent form, and speak one of the languages into which the consent form and data collection instruments have been translated, including English, D’Luo and Kiswahili.

Sources of Materials

Data for this study will be collected from several sources. Clinical and demographic data will be obtained through chart reviews and physical examination. We will also obtain clinical information from the colposcopic examinations. Information from the colposcopy and if performed, biopsy, will be entered into the participants’ medical records as it will be used to direct clinical care. We will also obtain cervical specimens for p16^INK4a^ and HR-HPV testing and vaginal wick specimens for women in the post-LEEP HIV-1 shedding study. These will be obtained solely for research purposes, and will therefore not be entered into the participant’s medical record. All data collection will take place in a private study room.

Potential Risks

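### The protocol gives contradictory accounts of how women are allocated to VIA or VILI, and mentions randomization only in the abstract; at 900 per test, sensitivity is known to about ±11 points, not ±5

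*Protocol*

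**What the plan says.** - **Abstract.** Randomization covers part of the cohort: "We will also randomize a small subset of women to undergo VIA compared to" VILI. No size or ratio is given.
- **Statistical Considerations and Sample Size Calculation, Specific Aim 1.** For a sensitivity of 75% within 5 points either way, "we will need to complete sequential VIA and colposcopy in" 1,800 women. The next paragraph splits the same total: "we will use the estimate of 1,800 women (900 VIA and 900 VILI to account for laboratory and sampling error) to power our study".
- **Study Design, Specific Aims 1, 2, 2a and 2b.** "Each participant will undergo a VIA or VILI with specimen collection". The section refers to a VILI arm, in which colposcopy comes first, but has no assignment rule.
- **Exclusion criteria.** Unsatisfactory VIA is a general exclusion, with the rationale "Woman would require alternative screening method (cytology, colposcopy or endocervical sampling) per WHO protocol". There is no VILI counterpart.
- **Ethical Considerations, Human Subjects Involvement.** Women in the cross-sectional study must "have a satisfactory Visual Inspection with Acetic Acid (VIA").
- **Subject recruitment and enrollment.** Women are recruited sequentially, and "participant numbers will be assigned after VIA and colposcopy".
- **Statistical Analysis, Specific Aim 1.** CIN2/3 prevalence is taken as 7%, confidence limits are exact binomial, and the two modalities are compared by McNemar's test.
- **Hypotheses (Null), item 1.** VIA, VILI and p16 are hypothesized to perform equally well, so comparing the tests is a stated purpose.

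**The concern.** A randomized small subset and a 900/900 split of the whole cohort cannot both be carried out. The surrounding text does not settle the matter. A woman given only VILI cannot show a satisfactory VIA, and McNemar's test has no paired results to work on if each woman has one test. Participant numbers issued after the examinations cannot determine which test was done during them.

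Two things are at stake. First, VIA and VILI are compared between different women, so a difference in sensitivity or specificity can be attributed to the test only if assignment did not depend on who the women were. Random assignment secures that, and the recruitment, design, procedure and visit sections do not mention it. Second, the number of CIN2/3 cases behind each sensitivity estimate depends on the allocation, so the precision that Aim 1 promises cannot be read from the protocol until the allocation is fixed.

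**Working it through.** **Inputs.** Sensitivity 75%, half-width 5 points, two-sided alpha 0.05, total 1,800, split 900/900 (Aim 1 sample-size text). CIN2/3 prevalence 7% and exact binomial limits (Statistical Analysis, Specific Aim 1).

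**1. The protocol's own figure.** Women with disease needed = 1.96² × p(1 − p) / d² = 3.8415 × 0.75 × 0.25 / 0.05² = 288.1. Dividing by 0.07 gives about 4,116 women. The stated 1,800 is not reproduced by this formula. It would correspond to a prevalence of 288.1 / 1,800 = 16.0%.

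**2. Sensitivity precision under each account of the allocation.** Cases = women × 0.07. The normal half-width is 1.96 × √(0.75 × 0.25 / cases). The exact (Clopper-Pearson) half-width uses the nearest count to 75%.

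| Allocation | CIN2/3 cases | Normal half-width | Exact 95% half-width |
| --- | --- | --- | --- |
| VIA in all 1,800 | 126 | ±7.6 points | ±7.9 points (94/126) |
| 900 per test | 63 | ±10.7 points | ±11.3 points (47/63, interval 62% to 85%) |
| Small subset | not computable | – | – |

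The last row is empty because no size is given. Neither computable row reaches ±5.

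**3. Specificity.** With 900 per test, 900 × 0.93 = 837 women are without CIN2/3. At 80% the half-width is 1.96 × √(0.16 / 837) = ±2.7 points, inside the stated ±5. The shortfall therefore concerns sensitivity only.

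**4. Detectable difference in sensitivity, 63 cases per arm, unpaired.** Power = Φ((|p1 − p2| − 1.96 × se0) / se1). Here se0 = √(2 p̄(1 − p̄) / 63), se1 = √((p1(1 − p1) + p2(1 − p2)) / 63), p1 = 0.75, and p̄ is the mean of p1 and p2.

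- p2 = 0.51: se0 = 0.0860, se1 = 0.0833; (0.24 − 0.1686) / 0.0833 = 0.857; power 80%.
- p2 = 0.93: power 79%, just short.
- p2 = 0.94: se0 = 0.0645, se1 = 0.0622; (0.19 − 0.1264) / 0.0622 = 1.02; power 85%.

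In whole points, the smallest detectable difference is 24 downward or 19 upward. The exact upward crossing is 0.932, about 18 points. A difference of 75% against 85% has 29% power.

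**5. Allocation and analysis side by side.** McNemar's test uses women whose two results disagree. Under Study Design each woman has one result, so there are no such pairs. The test fits only if both examinations are done in each woman, which Study Design does not provide for.

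**The case against.** The strongest reply is that the body of the protocol is more coherent than the abstract. The aims, Study Design, procedures and visit sections all give one test per woman, the sample-size text prints 900/900, and the abstract supplies the randomization. On that view the phrase about a small subset is a leftover, and sequence generation can sit in the study manual. Much of this stands. The 900/900 figure is there, so the size is contradicted rather than absent, and the mechanics of the list can live elsewhere. Whether women are randomized, how many, and who receives which test belong in the protocol.

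It is also fair that estimating each test's own accuracy against colposcopy does not require randomization. Only the comparison does.

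Several stronger readings are tempting and not supported:

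- *The protocol describes three different trials.* The sentence about VIA in 1,800 women reads as a sample-size calculation based on VIA; the analysis section says prior VIA estimates were used because they are more precise. The firmer sign that VIA is expected of everyone is the satisfactory-VIA criterion.
- *Tests will be allocated by clinic, clinician or period.* The design section is silent; it neither describes such a scheme nor denies randomization.
- *VIA and VILI have different readers.* The different clinician is the colposcopist, as against the VIA or VILI examiner.
- *Detectable differences are 50 points or more in a small subset.* Such figures rest on subset sizes that the protocol does not give, and the normal approximation is poor with a dozen cases or fewer per arm.

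**Conclusion.** The allocation is contradictory as written and needs to be reconciled. The abstract's randomized subset conflicts with the 900/900 split, the satisfactory-VIA criterion conflicts with a VILI-only arm, and McNemar's test conflicts with one test per woman. Random assignment, the only protection for the VIA/VILI comparison, appears in the abstract alone. With 900 per test, sensitivity is estimated to about ±11 points rather than ±5 (about ±8 even if VIA were done in all 1,800). The comparison can detect only differences of about 24 points below or 19 above 75%. These sizes assume the protocol's 7% prevalence and 75% sensitivity and an unpaired two-sided 5% test with 80% power. The documents do not show that assignment will be biased; they leave it unspecified.

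**What to change.** - **Allocation.** Reconcile the abstract, the Aim 1 sample-size text and Study Design to one statement. The version that fits the existing numbers and the abstract's randomization is that all 1,800 women are individually randomized 1:1 to VIA or VILI, assigned after consent and before the examination. Concealment mechanics and any stratification by clinic are optional detail. If a small subset is really intended, state its size and ratio and correct the 900/900 text instead.
- **Sample-size sentence.** Reword the statement about VIA and colposcopy in 1,800 women so that it no longer implies VIA in everyone.
- **Eligibility.** Change the criterion in the exclusion table and in Ethical Considerations to a satisfactory VIA or VILI, and align the sentence on when participant numbers are issued.
- **Analysis.** Replace McNemar's test with an unpaired comparison of proportions: among women with CIN2/3 for sensitivity, and among women without it for specificity.
- **Precision.** Restate the Aim 1 sensitivity precision as about ±11 points per test.

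The cost is protocol wording, an allocation list and a less favourable stated precision. No extra women or procedures are needed, provided the ±5-point target for sensitivity is given up openly.

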**GLOSSARY OF ABBREVIATIONS**

AUC…………………………………………………………………………….…Area Under the Curve

CIN………………………………………………………….………..Cervical Intraepithelial Neoplasia

FACES…………………………………………………....Family AIDS Care and Education Services

HR-HPV……………………………………………………………...High-Risk Human Papillomavirus

LEEP…………………………………………………………Loop Electrosurgical Excision Procedure

NAAT………………………………………………………………..Nucleic Acid Amplification Testing

ROC………………………………………………………………………..Responder Operating Curve

STI………………………………………………………………………Sexually Transmitted Infections

UCSF………………………………………………………...…University of California, San Francisco

VIA……………………………………………………………….......Visual Inspection with Acetic Acid

**BACKGROUND**

Invasive cervical cancer has become a rare disease in developed countries, largely due to the success of organized screening programs coupled with safe and effective treatment of precancerous lesions. Few resource-limited countries, however, have the funds or infrastructure for screening programs that detect and treat lesions before they progress to invasive cancer. The cytology-based screening programs which have substantially reduced the burden of cervical disease in developed countries are not feasible in resource-limited countries for several reasons.^1, 2^ They are costly, have high infrastructure requirements and necessitate multiple visits, which can lead to high rates of loss-to-follow up.^3-5^ Of the almost 500,000 new cases of cervical cancer diagnosed annually, 80% occur in developing countries.^1, 6^ In sub-Saharan Africa, women have a 2% to 4% lifetime risk of the disease.^1, 7^ Mortality from cervical cancer is much greater in resource-limited countries, because women are diagnosed at later stages and treatment options are limited. Cervical cancer carries an overall 80% five-year mortality rate for women in Sub-Saharan Africa, four times the rate of countries with organized screening programs.^8^ In Kenya, cervical cancer is the most common cancer among women, attributable largely to the lack of a national prevention program.^8, 9^ The exact incidence is unknown, but is estimated at approximately 40-200 per 100,000 women annually, with a two-to-threefold increase in HIV-positive women.^8, 10, 11^

Cervical cancer is an AIDS-defining malignancy, and HIV influences the risk for cervical cancer through multiple biologic pathways.^12^ HIV increases the incidence and persistence of infection with oncogenic human papillomavirus (HPV), the causative agent in cervical dysplasia cancer.^13-17^ HIV-infected women have a higher incidence and prevalence of cervical dysplasia and invasive cancer, a younger age of onset, present with more advanced malignancies and have lower survival rates than HIV-negative women.^11, 18-23^ Worsening HIV related immunosuppression is associated with more severe cervical lesions and disease progression.^24-26^ Recurrence of cervical lesions is much more common among HIV-infected than uninfected women,^27-30^ making follow-up essential for the prevention of invasive disease. The vast majority of women infected with HIV live in resource-limited settings with poor healthcare infrastructure, most notably in Sub-Saharan Africa. In these settings, limited access to cervical cancer screening programs puts them at even higher risk for cervical cancer related morbidity and mortality.^31^ HIV prevalence in Kenya was estimated to be between 4.9 and 7.3% at the end of 2007, with a prevalence in women aged 18-49 of 8.9%.^32, 33^ Before the widespread availability of anti-retroviral therapy, AIDS related deaths posed a much greater risk than cervical cancer. As the infrastructure for HIV treatment improves, women at highest risk for development of cervical disease are gaining access to the care and services that could facilitate cervical cancer prevention programs. HIV-clinics may represent the ideal setting for cervical cancer screening. To make an impact, screening and treatment strategies must be safe, low-cost and effective in HIV-infected women.

One strategy that has been proposed as a low-cost alternative to cytology screening is visual inspection of the cervix after application of 3-5% acetic acid (VIA). The technique is easily learned, has minimal infrastructure requirements and results are available immediately, allowing it to be coupled with same day treatment.^34, 35^ Several large trials have validated VIA as an effective screening method with the potential to decrease cervical cancer incidence and mortality.^36-38^ In HIV-negative women, VIA has been shown to have a similar sensitivity and specificity to HR-HPV testing and pap smears.^39-42^ However, unlike cytology screening, there have been no studies to evaluate the sensitivity and specificity of VIA in HIV-infected women.^43-47^ One of the potential drawbacks of using VIA in a see-and-treat program, however, is the undefined, but potentially high, false positive rate for cervical intraepithelial neoplasia 2/3 (CIN2/3), a precancerous lesion.^48^ Because this may lead to overtreatment, and potentially to increased infectivity, this needs to be defined in a rigorous study in a population of HIV-infected women.

In addition to low-cost, low-technology strategies for cervical cancer screening, rapidly increasing knowledge about the disease process that leads from persistent infection with HR-HPV to cervical dysplasia and cervical cancer has lead to the search for biomarkers that signal the dysplastic transformation of infected cells. Biomarker testing, either through immunohistochemical (IHC) staining of biopsy specimens or molecular assays could be used for screening or follow-up of at-risk women, triage of abnormal pap smear results or confirmation of histologic diagnoses. An ideal biomarker would be easy to collect and interpret, have a high sensitivity and specificity for precancerous lesions and could be processed with relatively simple technology in resource-limited settings. Availability of a biochemical assay for cervical dysplasia that could potentially be self-collected and read on-site would lower the costs, infrastructure and training needed for the collection and interpretation of cervical cytology specimens. One of the most promising new biomarkers undergoing evaluation is p16^INK4a^, a cyclin-dependent kinase inhibitor that is over-expressed in HPV-transformed cells.^49^ Studies among HIV-negative women have shown that IHC staining for p16^INK4a^ is strongly positive in virtually all invasive cervical cancers and is highly correlated with CIN2/3.^49^ In contrast, CIN1, which is thought to reflect transient HPV infection rather than precancerous changes, rarely stains positively for p16^INK4a^ on IHC.^50^ Therefore, presence of p16^INK4a^ on IHC may help further define abnormal lesions as high- or low-risk for cervical cancer, helping clinicians to determine which lesions need treatment. The addition of p16^INK4a^ IHC staining has been shown to improve inter-observer agreement for the diagnosis of CIN, and has been used in resource-limited settings to improve the reliability of the histological diagnosis, which is the gold-standard for making treatment decisions.^51^

A novel biochemical assay for p16^INK4a^ has been introduced that can measure biomarker levels directly from a swab of exfoliated cervical cells, rather than through the staining of cytology or biopsy specimens.^52^ The assay has been shown to have a high correlation for precancerous lesions, similar to IHC.^53^ A scoring system for the presence of p16^INK4a^ positive cells in immunocytochemistry (ICC) and biopsy specimens has been developed that increases the sensitivity (95-100%) and specificity (82-84%) for high-grade lesions.^54^ A protein-based assay with a dichotomous result for high-grade lesions has the potential to serve as a point-of-care test, which could be used as a stand-alone screening test or as an adjunct to increase the specificity of positive VIA. Although p16^INK4a^ has shown promise among HIV-negative women in resource-rich settings, to our knowledge there have been no studies testing the use of the biochemical assay among HIV-infected women or women receiving care in resource-limited settings. With this study, we seek to establish the feasibility of p16^INK4a^ biochemical assay in an HIV-clinic in a resource-limited setting, and to characterize the performance of a p16^INK4a^ biochemical assay among HIV-infected women. In addition, we will compare the test characteristics of p16^INK4a^ with the only other biomarker that is currently feasible as a point-of-care test, high-risk HPV (HR-HPV). We anticipate that this will be the first step towards the introduction of an assay that can be used as a stand-alone point-of-care screening test for cervical cancer for an extremely high-risk and vulnerable population: HIV-infected women in resource-limited settings.

Another important factor to consider in prioritizing the diagnosis of cervical dysplasia and cervical cancer in HIV-infected women is the potential for increased infectivity related to presence, diagnosis and treatment of cervical disease. This is especially important in countries such as Kenya, where HIV-prevention strategies remain paramount as healthcare resources and access to anti-retroviral therapy remain limited and the majority of infected individuals are in relationships with HIV-negative partners.^33, 55^ Understanding factors impacting HIV-transmission risk is essential to developing and implementing effective prevention strategies. The presence of HIV-1 in the genital tract plays a large role in the heterosexual and maternal-to-child transmission of HIV. ^56, 57^ The association between sexually transmitted infections (STIs) and increased risk of HIV transmission has been well studied and is thought to be partly attributable to increased levels of HIV-1 found in secretions of co-infected individuals.^58-60^ Herpes simplex virus type-2 co-infection is associated with the greatest increase in cervicovaginal HIV-1 shedding, even in the absence of genital ulcers.^61^ Increased shedding has also been seen with bacterial vaginosis,^62, 63^ *Chlamydia trachomatis*,^64^ *Neisseria gonorrhea*,^65^ *Candida* and nonspecific vaginitis.^66, 67^ Despite the high prevalence of HR-HPV, cervical dysplasia and cancer in this population, remarkably little is known about the relationship between HR-HPV-related lesions, treatment of these lesions and HIV-1 genital shedding. One prospective study among 124 HIV-infected women showed an up to 4-fold risk of HIV-1 RNA in the genital tract among women with HR-HPV, with no significant relationship to CIN. Limitations to this study include a high prevalence (50%) of cervical and vaginal infections and no participants on anti-retroviral therapy. A later study by the same investigators showed a two-fold increased risk of HIV-1 shedding among women with CIN, after controlling for plasma levels of HIV, CD4+ count and vaginal infections.^68^ A better understanding of the impact of CIN on HIV-1 genital shedding may provide additional rational for implementing screening programs in populations at high-risk for both cervical cancer and HIV transmission.

In addition, little is known about the level of HIV-1 shedding in cervix after biopsy and treatment for dysplasia. When planning for safe and effective cervical cancer prevention strategies, clinicians and investigators should consider the potential impact of CIN diagnosis and treatment on HIV-1 genital shedding. Studies have shown that the presence of inflammatory markers and cytokines in the cervix is associated with increased HIV-1 in cervicovaginal secretions,^69, 70^ although little is known about the relevance of these findings to the post-biopsy and post-LEEP cervix. Post-treatment cytology specimens have decreased specificity due to obscuring inflammatory markers related to thermal damage and repair for up to four months after the procedure.^71, 72^ The prolonged presence of inflammatory markers suggests the possibility of increased HIV-1 in cervicovaginal secretions throughout that period. Women are typically counseled to remain abstinent for one month after treatment with LEEP to reduce the potential risk of infection or bleeding. A study from South Africa found that at least 50% of participants reported resumption of sexual intercourse within two weeks of undergoing LEEP or cryotherapy for treatment of cervical dysplasia.^36^ Increased HIV-1 secretions in the genital compartment after treatment for cervical dysplasia, combined with high levels of early post-treatment intercourse could place a significant number of partners at higher risk of HIV acquisition. To our knowledge, there has been only one study evaluating HIV-1 genital shedding after treatment for cervical dysplasia. That study by Wright, et al, showed an average *increase* of up to 10,000 copies of HIV-1 RNA in the cervicovaginal secretions post-treatment, with less than 1% attributable to the presence of blood in the genital tract.^73^ There were only fourteen women in the study, three of whom had cryotherapy and eight who had undergone LEEP. Gains in efficacy against cervical dysplasia may be offset by increased risk for infectivity if a method is associated with significantly greater duration and magnitude of HIV genital shedding.

The study described below will provide important information that can be used in the design and prioritization of an effective, resource-appropriate screening program. We seek to clearly define the test characteristics of two novel, but very different screening approaches that can be employed in resource-limited settings. We will then determine the magnitude of difference in HIV genital shedding between women with and without CIN2/3, and then explore the effect of diagnosis of as well as treatment for CIN2/3 on that shedding. The information gained from the research we carry out will provide a critical foundation in the effort to safely and effectively diagnose and treat cervical dysplasia among HIV-infected women in resource-limited settings, working toward prevention of cervical cancer in this population.

